#### BeUpstanding Website

The BeUpstanding program is delivered via the BeUpstanding Champion Toolkit hosted on the BeUpstanding website [27]. The website is hosted, maintained, and updated by project staff, with all data stored in a secure, cloud-based system (Microsoft Azure) that is backed up weekly to the University of Queensland servers (lead investigator’s team: [name]). The toolkit itself is powered through a bespoke platform that includes in-built systems that facilitate survey design, project management, and user tracking, enabling the research team to readily track a champion’s progress and engagement through the program and collect survey-based data. In addition to the toolkit, the BeUpstanding website (freely available) also includes pages on the business case and associated promotional materials for running the BeUpstanding program, the evidence base supporting the BeUpstanding program, a checklist to ensure program readiness, a link to the BeUpstanding blog and social media, a frequently asked questions section, and details on the investigators and partners. Champions are encouraged to visit the blog via monthly electronic newsletters for the latest research evidence and tips for running the program.

## Methods

### Aims and Research Questions

The aim of this study is to evaluate the BeUpstanding program in the context of a national implementation trial. The research questions to be answered are those important to informing the dissemination (phase 5) [13]: in particular, who takes part in the program, how the program was delivered, did the program work (and for whom did it not work), and how much did it cost. The RE-AIM (Reach, Effectiveness, Adoption, Implementation, and Maintenance) Framework [49] will be used to guide the evaluation, with assessment of the *adoption/reach* of the program (the number and characteristics of work teams and participating staff), program *implementation* (completion by the champion of core program components), *effectiveness* (on workplace sitting, standing, and moving), and *maintenance* (sustainability of changes). The implementation trial is funded by a National Health and Medical Research Council (NHMRC) of Australia Partnership Project Grant (number 1149936), which includes cash and/or in kind support from the five partners (see below). Ethical approval was gained by The University of Queensland Human Research Ethics Committee (approval number 2016001743). The trial was prospectively registered on May 12, 2017 (ACTRN12617000682347), before the soft launch of the program and last updated on the June 11, 2019. All participants will provide informed consent to participate.

### Study Design

A single-arm design will be used to evaluate the BeUpstanding program, with repeated cross-sectional evaluations at preprogram (0 weeks), end of program (approximately 8 weeks; primary endpoint), and at 9 months postprogram (approximately 12 months post sign up). Repeated cross-sectional evaluations provide a flexible evaluation protocol [50] that can assess change within retained members of the baseline survey cohort over time and more general time trends (owing to both changes over time within participants and some fluidity in work team membership, such as because of workforce turnover).

### Study Eligibility and Accrual Targets

On the basis of data reported by the champion as part of the web-based registration process, eligible Australian-based work teams will be those who had not run the BeUpstanding program previously with a minimum of five staff members, job roles or tasks that predominantly involve desk-based work, and a staff member willing to perform the duties of a workplace champion. Champions must also be planning to run the program within the recruitment window. For large organizations, including those located across numerous sites, multiple work teams from the one organization will be eligible to participate. These will be treated as a single combined *team* when the intervention is concurrent and within a workplace as per the criteria; otherwise, separate teams will be permitted to participate. Each champion will invite all employees within their work team to participate in the program and its evaluation. All workers invited will be considered eligible unless they indicate within the staff survey that they are unable to currently walk or stand for at least 10 min without an assistive device or requiring assistance from another person. Accrual targets have been set at 50 or more work teams per priority sector and 10,000 or more staff exposed to the program in total (see sample size). Performance against these accrual targets will be reviewed at the quarterly steering committee meetings, with the promotion and marketing plan adapted as required to ensure targets are met.

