### BeUpstanding Program

The BeUpstanding program is designed to be implemented within a workplace (broadly, defined as from one organization, with the same workplace policies) by a champion to their work team (colocated members of the workplace) of which the champion is also a member. Larger workplaces may run BeUpstanding by having several champions deliver the intervention to their teams concurrently. For the purposes of accrual targets and statistical analyses, these multiple teams are counted as one combined *team*. There are three phases to the program (plan, do, and review) and five steps as part of the BeUpstanding program (Table 1). Each step has associated tasks for the champion to complete, noting that not all tasks may be relevant for all champions because of their workplace and/or work team requirements. The toolkit provides information (*training*) on the purpose of each step and task and resources to support the implementation of each task. As part of the implementation trial, champions will receive further training via coaching calls. The most critical step of the program is the staff workshop (Step 3.3). This step is designed to get everyone in the work team on board in terms of why and how the team can BeUpstanding together. In line with participatory design principles [41], work teams are encouraged to collectively choose three strategies to stand up, sit less, and move more to implement, based on which best suit their team’s needs and existing culture. Some strategy suggestions, according to the hierarchy of control [42], are provided within the toolkit (Table 2 shows a modified version of this resource). Staff members may choose to implement more than the three team strategies. Alternate suggestions for raising awareness and enabling this collective decision making are provided when running the workshop with all staff at the same time is infeasible (eg, because of shift work). Champions are encouraged to run the BeUpstanding program for 8 weeks from the launch, sending emails and rotating posters on a weekly basis for the first 4 weeks and fortnightly for the second 4 weeks, with the posters and emails organized according to the recommended schedule. Collectively, the workshop, posters, and emails are designed to raise awareness of the benefits of sitting less and moving more, build a supportive culture for change, and encourage participants to take action to achieve this change. Owing to the participative nature of choosing the strategies, and the ability of the champion to tailor the emails, the actual intervention program is bespoke for each work team. The champion is responsible for running and evaluating the program, which includes sending all staff in their work team links to the web-based evaluation surveys (Task 2.2; Task 5.1). Champions are also encouraged to hold staff events (eg, a lunchtime walk and wear your sneakers to work day) and to celebrate and promote individual and whole-of-team success. All staff in the work team will potentially be exposed to the intervention messages (posters and emails), and all staff can choose their level of involvement with both the strategies and the evaluation components. The toolkit encourages champions to run BeUpstanding (or components of thereof) with their team on an annual basis.

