**Figure 1 figure1:**
[figure not shown]
Key actions, data collected, and data collection method of the BeUpstanding implementation trial. Staff focus groups will be conducted in a sub-sample of teams only; separate consent will be sought from staff members for participation in this component.

The promotional activities undertaken by partners will be recorded at the 6-weekly partner meetings, with their impact on registrations tracked through the analytics in the toolkit website. The promotional pathways will be tracked through URL identifiers, through Google Analytics, and via champion self-reporting through the champion profile survey. Factors potentially influencing uptake and engagement with the program (eg, number of teams within a workplace participating in the program) will also be tracked via the registration survey and implementation checks. To ensure minimum data accrual targets are met, the project manager will follow up with champions (via email/phone) where necessary to encourage and support data collection.

The project manager will have a minimum of five telephone contacts with the champion across the implementation trial evaluation: (1) recruitment, (2) confirmation of consent and explanation of next steps, (3) as soon as possible following the staff workshop, (4) at the end of the program, and (5) 9 months after the end of the program. Focus groups will be undertaken with a subsample of consenting staff from participating teams (n was approximately 15) at the end of the program to assess their perspectives on the processes and outcomes of the program. A mix of teams who made small/no, midrange, and large improvements and from different sectors will be purposively sampled, with focus groups conducted either in person or on the web via a virtual meeting room.

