#### Data Analyses

Adoption, reach, and implementation outcomes will be described overall and within each priority sector. Effectiveness outcomes will also be evaluated overall and within each priority sector, with all work teams that are located in multiple sectors (eg, regional and small businesses) examined as part of every sector to which they belong. Effectiveness outcomes collected at the end of program only from champions and/or staff (eg, satisfaction) will be described. Effectiveness of the intervention on the primary outcome and secondary outcomes (continuous) collected repeatedly in the staff surveys will be assessed using mixed models that account for nonindependence in the form of individuals with repeated observations (baseline, end of program, and postprogram) and *team* clustering. The primary endpoint is the end of program (approximately 8 weeks). The pragmatic aspects of the champion-led collection of anonymous data from staff within a workplace means the staff surveys will be sent out to all staff who are team members at the time in a repeated cross-sectional fashion. Most are likely a core cohort sent all surveys (not known to the research team) who may respond to none or any number of the three surveys. In addition, some team members will be added or lost with workforce turnover. Accordingly, the evaluation will consist of assessing both changes within baseline responders who are followed up over time, and as this may be a select motivated subset, also assessing time trends in all evaluable cases (responders to any survey). Time trends will be considered both unadjusted and adjusting for potential compositional differences between responders at each assessment (because of variations in team membership with workforce turnover and who responds to each survey). To evaluate sensitivity of conclusions to missing data handling, multiple imputation analyses will also be performed. Team-level variation in effectiveness will be considered. If applicable, then program engagement, characteristics of the work teams and workplace champions, and the timing (month/year) of the intervention will be explored as reasons for the differential effectiveness.

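### Separate teams from one organization may enrol, but the model and sample size name no level above the team, so correlation between them is ignored

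*Protocol article*

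**What the plan says.** Study Eligibility and Accrual Targets states that, for large organizations including multi-site ones, "multiple work teams from the one organization will be eligible to participate". These become one unit "when the intervention is concurrent and within a workplace as per the criteria; otherwise, separate teams will be permitted to participate". The BeUpstanding Program section describes delivery "within a workplace (broadly, defined as from one organization, with the same workplace policies"), and says of larger workplaces whose champions deliver concurrently: "For the purposes of accrual targets and statistical analyses, these multiple teams are counted as one combined" team.

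Data Analyses assesses the repeatedly measured effectiveness outcomes, overall and within each priority sector, with "mixed models that account for nonindependence in the form of individuals with repeated observations (baseline, end of program, and postprogram) and *team* clustering". It names no workplace or organization level.

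Sample Size for Primary Effectiveness Outcome gives 47 to 62 teams for 80% to 90% power. It assumes five workers per team, SD 90, r = 0.5 and one intracluster correlation of 0.1. From this it sets a minimum of 50 teams in every priority sector.

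Data Collection says that the "number of teams within a workplace participating in the program" will be tracked, but as a factor that may influence uptake and engagement, not as a clustering level.

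**The concern.** Two groups of related teams escape the merging rule: teams in one workplace that run the program at different times, and teams in different workplaces of one organization. The first group shares policies by the protocol's own definition of a workplace, and a later start does not remove that. The second group may share senior management, and policies to some extent.

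Change could be correlated across such teams because part of the program works above the team. Management commitment is the first step, organizational support must be confirmed before trial entry, and the behavioral targets are pursued mainly through organizational, environmental and social approaches.

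A model that stops at the team treats these teams as independent. If their changes are correlated, the standard error of the mean change is too small and the test rejects too often. The sector analyses are the most exposed, because each is planned around only 50 teams.

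**Working it through.** **Inputs from the sample size section:** difference d = 20 min per 8 hours; SD 90; r = 0.5; m = 5 workers per team; intracluster correlation 0.1; two-sided 5%.

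**Inputs assumed, because the protocol does not give them:** q, the number of separate teams per organization (1.25 to 5), and ρ, the correlation in change between workers in different teams of one organization (0.01 to 0.05).

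**Step 1. Reproduce the plan's figure.**
- SD of change = 90 × √(2 × (1 − 0.5)) = 90.
- Design effect = 1 + (5 − 1) × 0.1 = 1.40.
- Teams = [(z for alpha + z for power) × 90/20]² × 1.40/5. The normal approximation gives 44.5 (45) for 80% power and 59.6 (60) for 90%.
- With the noncentral t distribution on teams − 1 degrees of freedom, the results are 47 and 62, exactly as stated. Power with 50 teams is 82.9%.

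The plan's figure is therefore right on its inputs, and it rests on one clustering level with independent teams.

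**Step 2. Add the organization level.** Keep the total within-team correlation at 0.1 and let ρ be the part shared across teams of one organization. At ρ = 0.05, half of the within-team correlation comes from the organization.
- Design effect = 1 + (m − 1) × 0.1 + m × (q − 1) × ρ = 1.40 + 5(q − 1)ρ.
- SE ratio (true to team-only) = √(design effect/1.40). The team-only SE is understated by 1 − 1/ratio.
- Type I error of the team-only test = 2 × [1 − Φ(1.96/ratio)].
- Power and required teams for an analysis that respects the organization use the noncentral t with teams/q − 1 degrees of freedom.

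Worked case, q = 3 and ρ = 0.05: design effect = 1.40 + 5 × 2 × 0.05 = 1.90; ratio = √(1.90/1.40) = 1.165; SE understated by 1 − 1/1.165 = 14%; type I error = 2 × [1 − Φ(1.682)] = 9.2%.

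| q | ρ | Design effect | SE ratio | SE understated by | Type I error, team-only | Power, 50 teams | Teams for 80% / 90% |
|---|---|---|---|---|---|---|---|
| 1.25 | 0.01 | 1.41 | 1.004 | 0.4% | 5.1% | 82.2% | 48 / 63 |
| 2 | 0.02 | 1.50 | 1.035 | 3% | 5.8% | 78.6% | 52 / 68 |
| 2 | 0.05 | 1.65 | 1.086 | 8% | 7.1% | 74.7% | 57 / 75 |
| 3 | 0.05 | 1.90 | 1.165 | 14% | 9.2% | 66.7% | 67 / 87 |
| 5 | 0.05 | 2.40 | 1.309 | 24% | 13.4% | 52.6% | 87 / 113 |

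The formula takes the same number of teams in every organization.

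**The case against.** The strongest reply is that the protocol already handles the most obvious dependence. Concurrent teams under the same policies are one unit for accrual and analysis, and the team in the model is most naturally read as that combined unit. This stands. A reader might infer that teams sharing management and policies are in general analysed as independent. The text does not support that: the gap covers only the two residual groups, and teams in different workplaces of one organization need not share policies under the protocol's definition.

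Second, much of the intervention varies by team. Each team chooses its own strategies, the staff workshop is called the most critical step, and the delivered program is described as tailored to each team. This argues for a modest ρ, but not for zero.

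Third, the protocol does not say how many organizations will contribute separate teams. The effect could be negligible, as the first row of the table shows. This also stands.

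Fourth, a condensed article may leave further random effects to the analysis plan. This carries less weight here. The article itself lists the forms of nonindependence that the model handles and fixes the unit of analysis, and its sample size reproduces only with independent teams. The stated specification is incomplete for a design that expressly admits several teams per organization.

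**Conclusion.** The point holds in a limited form. Separate teams of one organization are allowed, and neither the model nor the sample size has a level that captures correlation between them. Standard errors may be too small, chiefly in the sector analyses. Across the cases shown, the type I error is 5.1% to 13.4%, and power with 50 teams in a correct analysis is 82.2% down to 52.6%. These values rest on assumed q and ρ; the protocol supports no particular row.

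Three stronger readings go beyond the documents:
- A reader might infer that a sector could fill its 50 teams from very few organizations, or that some sectors consist mainly of large multi-site employers. Nothing in the protocol gives the number of organizations or their make-up by sector.
- A reader might infer that the 47 to 62 teams are miscalculated. They reproduce exactly.
- A reader might see harm in the absence of a sub-team level inside combined teams. Clustering on the combined unit already captures dependence at the higher level, and no loss of validity in the standard errors has been shown.

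**What to change.** In Data Analyses, state that the effectiveness models include organization above team, with a random intercept and a random change over time. If too few organizations contribute more than one team to estimate these, use standard errors clustered on organization instead. In each sector, report the number of distinct organizations beside the number of teams, so that the 50-team target can be judged against the independent units behind it.

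This needs an organization identifier. The protocol lists organization characteristics and the tracking of teams per workplace, but does not explicitly state such an identifier. Applying the merging rule already requires knowing which teams belong together. Staff records are matched in combination with the champion ID, so linking each champion to an organization would be enough and adds no question for staff.

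The cost is a change of wording, one extra data field and somewhat wider intervals where organizations contribute several teams. If almost every organization contributes one team, the results will barely change.

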### Study Partners and Promotion

The implementation trial will be conducted in partnership with five Australian workplace health and safety policy and practice organizations: Safe Work Australia, Comcare, Queensland Office of Industrial Relations, The Victorian Health Promotion Foundation (VicHealth), and Healthier Workplace Western Australia. These organizations are responsible for developing, implementing, and/or promoting Australian workplace health and safety policy. Each partner has committed to endorse and promote the toolkit across their relative jurisdictions. Desk-based employees from a wide cross-section of industries will be targeted, inclusive of sectors collectively identified as priorities by the partners (small business, regional, call center, blue collar, and government). To ensure efforts are coordinated, a detailed action-mobilization plan will be developed with the partners. The plan, which will include an annual promotional *push* via an awareness raising event, will build on and coordinate with existing communication channels and resources from the partners and participating institutes, including social media, web links, email listservers, newsletters, workplace health promotion and occupational health networks, conferences, and workshops.

### Study Protocol for the Implementation Trial

The BeUpstanding website [27] is designed for workplace champions; however, anyone can freely sign up to use the BeUpstanding Champion Toolkit via the registration survey (sign up form) on the BeUpstanding website. At signup, a user identifier is generated and a welcome email is automatically sent that includes details regarding the implementation trial. To unlock the toolkit contents, the user is required to complete the champion profile survey and is asked to nominate their intended role as a toolkit user (which might be a workplace champion or another nondelivery role, such as senior decision maker, interested staff member.). Following completion of this survey, champions with work teams that appear eligible for the implementation trial will be invited via a phone call from the research team to participate in the implementation trial, with recruitment continuing until accrual targets are met. This phone call with the champion will be used to confirm the eligibility of the work team for involvement in the implementation trial, ascertain from the champion the likely readiness of the work team to participate in the program, and confirm the contact details of the workplace champion (and an alternate contact). Those eligible and indicating interest in trial participation will be sent additional information on trial participation requirements, namely, confirmation of organizational support to run the five-step BeUpstanding program and commitment to the implementation trial evaluation components. The champion’s electronic consent to the trial will be required before implementation trial enrolment.

### Data Collection

Outcome and process data and the characteristics of the workplaces, champions, and staff taking part in the implementation trial will be collected via the dedicated, stand-alone BeUpstanding website (Registration Survey; Champion Profile Survey; Workplace Audit; Staff Surveys —baseline, end program, and maintenance; Strategy Survey; Program Completion Survey; and toolkit analytics) and by the project manager (implementation checks and qualitative interviews), as outlined in Figure 1. Champions will be required to provide informed web-based consent for their data to be used by the research team before completing the Champion profile survey, with further consent required to participate in the implementation trial. Staff will be required to provide informed consent for their data to be used by the research team before completing each of the staff surveys. Data for staff are anonymous; however, to enable participants to be tracked across data collection points, each staff survey includes three questions designed to generate a unique (but anonymous) identifier for the staff participant when used in combination with the champion ID: day of the month they were born on, first letter of mothers first name, and last three digits of their mobile number.

